### Study design, sample, and recruitment

#### Sample size

As a pilot study with no pre-specified effect size hypothesis, it is not relevant to estimate a sample size for hypothesis testing. However, to carry out preliminary analysis of impact, we defined the sample size as follows: assuming an intraclass correlation coefficient of 0.04, an effect size of 0.125 (index f) equivalent to Cohen’s d = 0.25, with a significance level of 5% and a statistical power of 80%, the minimum sample required would be 501 participants (167 per site, of three locations). Our goal is to recruit a minimum of 170 participants from each site, given an expected moderately high attrition rate.

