#### Study design

Our study is based on a cross-over design, whereby participants in three treatment municipalities (Florencia, Santa Marta, and Valledupar) will be offered the intervention, while participants in four control municipalities (Apartadó, Buenaventura, Ciénega, and San Andrés de Tumaco) will serve as control. Due to ethical reasons, we must offer the intervention to beneficiaries in the control municipalities following the period of intervention in the treatment group. Control municipalities will thus receive the intervention once the two post-treatment measures are taken.

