### Quantitative analysis of impact

Our primary aim will be to assess the impact of the intervention on our mental health and human capital outcomes. We will use regression analysis with a difference-in-differences design, which compares changes in outcomes before and after intervention measures across participants in treatment and control areas. This approach considers human capital as an outcome embodied in individuals by exploring the variation in individual knowledge (cognitive skills captured by academic performance) and individual abilities (non-cognitive skills acquired as life competencies). Thus, we will look at the magnitude of mental health-based rehabilitation on young adult students across different dimensions of mental health (depression and anxiety, fundamentally), which is considered beneficial due to human capital accumulation.

Since individual observations will be collected in different regions, we will adjust for clustered data. In the absence of treatment randomization that assures that treatment and control groups are exchangeable, this quasi-experimental design helps us to control for time-invariant differences between treatment and control areas by focusing on changes, rather than levels, in outcomes. To address bias from time-varying confounders, we will incorporate controls for time-varying factors in all analyses. We will all report the prevalence of depression, anxiety, and PTSD, along with their commodities and the effectiveness outcome, which will be the proportion of participants with a reduction in their baseline symptoms. To determine the changes in human capital, we will use both administrative and survey data that measure continued JeA program enrolment, accumulated grade point average, and self-reported hours dedicated to study. This will be carried out in STATA-19.

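### The sample size of 501 names an ICC of 0.04 but matches a calculation without clustering, so the stated 80% power does not follow for three against four municipalities

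*Protocol article*

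**What the plan says.** The Sample size section of the Protocol article first says that a pilot without an effect hypothesis set in advance needs no sample size for testing. It then gives one for a preliminary impact analysis: "assuming an intraclass correlation coefficient of 0.04", "an effect size of 0.125 (index f) equivalent to Cohen’s d = 0.25", 5% significance and 80% power. The result is that "the minimum sample required would be 501 participants (167 per site, of three locations". The recruitment target follows: "Our goal is to recruit a minimum of 170 participants from each site, given an expected moderately high attrition rate".

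The Study design section allocates by whole municipality. Three municipalities are offered the intervention, and "participants in four control municipalities" serve as comparison. The section on quantitative analysis of impact calls the impact assessment the primary aim, plans a difference-in-differences regression, and states: "Since individual observations will be collected in different regions, we will adjust for clustered data".

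**The concern.** An ICC above zero raises the number of people needed when whole municipalities are allocated. The figure of 501 looks like the number for a plain two-group comparison of individuals, as if the ICC had been listed but not used. The total is also divided over three locations, although the comparison involves seven municipalities. The relation between f = 0.125 and d = 0.25 holds for two equal groups, so 501 reads as a two-arm total, yet it is spread over what could be the treated sites alone.

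At stake is how the impact result will be read. With few municipalities, their number can limit power more than the number of people does. If readers believe that the study had 80% power for d = 0.25 when it had much less, a null result could be taken as evidence against the intervention.

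**Working it through.** **Inputs from the article.** ICC ρ = 0.04; d = 0.25 (f = 0.125); α = 0.05; power 80%; N = 501 = 3 × 167; recruitment goal 170 per site; 3 treated and 4 control municipalities.

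**Assumptions made here.** Two-sided test; outcome SD of 1; ρ acts between municipalities; equal numbers per municipality; no attrition.

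**1. Reproducing 501.** Without clustering, the two-group total is 4 × [(1.960 + 0.842)/0.25]² = 502.3, or 252 per arm and 504 in total. The F test with two groups needs 505, and its power at 501 is 79.7%. So 501 lies at, or just below, the unclustered minimum, and in a plain two-group comparison any design effect above 1 would push the requirement past it. Other routes do not give 501:

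- one-sided test: 396
- one-way ANOVA with f = 0.125: 620 (3 groups), 702 (4 groups), 879 (7 groups)
- repeated-measures ANOVA with 0.04 as the correlation between 2 or 3 measures: 183 to 460

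**2. Post-treatment comparison of 3 v 4 municipalities with ρ = 0.04.** With m people per municipality, Var = {[1 + (m − 1)ρ]/m} × (1/3 + 1/4). The t reference has 7 − 2 = 5 df.

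- 501 in total, m = 501/7 = 71.6: design effect 1 + 70.6 × 0.04 = 3.82; Var = (3.82/71.6) × 0.5833 = 0.0312; SE 0.177; power 21% (t) or 29% (normal).
- 170 in each of seven (an assumption; 1,190 people): design effect 1 + 169 × 0.04 = 7.76; Var = (7.76/170) × 0.5833 = 0.0266; SE 0.163; power 24% or 33%.
- Unlimited m: Var = 0.04 × 0.5833 = 0.0233; SE 0.153; power 27% or 37%. This is the ceiling for this comparison.

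**3. The planned difference-in-differences.** Differencing removes the part of a municipality's effect that stays constant. Let r be the correlation over time within an individual and c the correlation over time of municipality effects; the article gives neither. Then Var = 2 × [ρ(1 − c) + (1 − ρ)(1 − r)/m] × 7/12. For example, with m = 71.6, r = 0.5 and c = 0.9: 2 × [0.004 + 0.48/71.6] × 0.5833 = 0.0125, SE 0.112.

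The minimum detectable effect (MDE) at 80% power is 2.80 × SE (normal: 1.960 + 0.842) or 3.51 × SE (noncentral t, 5 df). With r = 0.5:

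| People | c | SE | Power for d = 0.25, t / normal | MDE in SD, t / normal |
|---|---|---|---|---|
| 501 in total | 0.5 | 0.177 | 21% / 29% | 0.62 / 0.49 |
| 501 in total | 0.8 | 0.131 | 34% / 48% | 0.46 / 0.37 |
| 501 in total | 0.9 | 0.112 | 44% / 61% | 0.39 / 0.31 |
| 501 in total | 1.0 | 0.088 | 62% / 81% | 0.31 / 0.25 |
| 170 in each of seven | 0.5 | 0.163 | 24% / 33% | 0.57 / 0.46 |
| 170 in each of seven | 0.8 | 0.112 | 44% / 60% | 0.39 / 0.31 |
| 170 in each of seven | 0.9 | 0.089 | 61% / 80% | 0.31 / 0.25 |
| 170 in each of seven | 1.0 | 0.057 | 93% / 99% | 0.20 / 0.16 |

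A higher r helps. With r = 0.7 and c = 0.95, 170 in each municipality gives 86% (t) or 97% (normal). With r = 0.7 and c = 1.0, 501 in total gives 83% or 95%.

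**The case against.** Three arguments weigh on the other side.

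**It is a pilot.** The article says that a sample size for testing is not relevant and calls the impact analysis preliminary. This lessens the consequence. It does not correct a printed power figure, and the analysis section makes impact the primary aim and says that clustering will be adjusted for.

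**Difference-in-differences removes stable municipality effects.** This stands, and it limits the point. A reader might infer that seven municipalities cannot deliver 80% power at all, or might take the post-treatment power of 24% as the headline. The documents support neither. The post-treatment comparison is not the planned analysis, and with constant municipality effects the planned one reaches 93% or more at 170 per municipality. But the article states no correlation over time, and this route is not shown as the source of 501.

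**The article leaves the ICC undefined.** It does not say whether 0.04 applies to municipalities or to another unit, or to levels or to changes. It follows that 501 cannot be declared with certainty to be the unclustered total; it matches that total. A reader might also apply the design effect for 167 per site to the 501 and treat the result as two equal arms. No layout in the article fits that, since three equal sites cannot form two equal arms. Likewise, 170 in each of seven municipalities is one reading of the recruitment goal, not a stated layout.

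**Conclusion.** The point holds in a conditional form. The listed inputs, including ICC 0.04, do not lead to 501; the only match found leaves the ICC out. The split over three locations does not fit the seven municipalities, and the number of controls is not clear.

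Whether 80% power is reached depends on quantities that the article does not give. For the planned analysis with r = 0.5, power for d = 0.25 ranges from about 21% to 81% with 501 people in total and from about 24% to 99% with 170 in each of seven, over c from 0.5 to 1.0 and both reference distributions. It reaches 80% only when municipality effects are nearly constant over time. With the t reference and r = 0.5, 501 people fall short even then (62%). All of this assumes that 0.04 is a between-municipality ICC at each time point and that nobody is lost.

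**What to change.** Rewrite the Sample size paragraph:

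- Say that 501 matches a two-group calculation without clustering, or show how the ICC entered. Define the unit of the ICC and whether it refers to levels or to change.
- Reconcile the three locations with the seven municipalities, and give planned numbers for the control sites.
- Replace the unqualified 80% with power and minimum detectable effect for the 3 v 4 difference-in-differences, over a stated range of individual and municipality correlations over time and with the reference distribution named.
- Present impact as estimates with confidence intervals.

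This costs one paragraph and needs no extra enrolment. The downside is that the stated power will look less favourable.

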### Digital mental health interventions in Colombia

There are few studies on the feasibility and impact of digital mental health interventions in Colombia. A recent study of an internet intervention for college students, assisted by a trained person, showed positive results but high dropout rates (around 80%) (19). Members of our team have developed and tested several simple mental health digital tools with good adherence and outcomes in other Latin American countries (20–23). With the advent of the COVID-19 epidemic, remote delivery is an additional underexplored challenge that this project aims to address. This study is particularly unique in that we work directly with Government within a public program. So far, no studies have assessed the impact of incorporating a mental health intervention within an existing public cash transfer program to address poverty.

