##### Intervention development

While the digital intervention was already established, the role out and launch of the study was developed in workshops and formative interviews. Previous interventions have shown that digital initiatives have a high dropout rate and are more effective when guided by coaches. To anticipate this possibility, we will hold a virtual workshop with stakeholders (six JeA central staff and four from the FSFB) to draw a joint Theory of Change plan and a clear plan of action to launch the pilot study (Phase 3). The main stakeholders involved in the intervention development are JeA beneficiaries and staff. We will aim to conduct this work in small groups of between 4 and 8 people for staff-only and beneficiaries-only discussions and 10–15 people for joint workshops, representing all the territories involved. Team members with experience in facilitating will plan each group session. These team members will also facilitate the workshops. Potential participants will be identified and recruited with the help of JeA staff members.

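### The recruitment goal of 170 per site allows for 1.8% attrition against the required 167, although the same sentence expects moderately high attrition

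*Protocol article*

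**What the plan says.** All the figures stand in the Sample size section of the protocol article. The assumptions are "an effect size of 0.125 (index f) equivalent to Cohen’s d = 0.25", a 5% significance level, 80% power, and clustering entered by "assuming an intraclass correlation coefficient of 0.04". The result is that "the minimum sample required would be 501 participants (167 per site, of three locations"). The next sentence sets the target: "Our goal is to recruit a minimum of 170 participants from each site, given an expected moderately high attrition rate". No attrition rate is given there or elsewhere in the article.

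Two other places bear on how much loss to expect. Under Digital mental health interventions in Colombia, the article reports dropout of around 80% in a Colombian internet intervention for college students. It also says that the team's own digital tools were well adhered to elsewhere in Latin America. Under Intervention development it says: "Previous interventions have shown that digital initiatives have a high dropout rate and are more effective when guided by coaches".

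Survey outcomes are collected online at baseline, at the end of the roughly 16-week intervention, and three months after that.

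**The concern.** The sentence offers 170 per site as the answer to a moderately high expected loss, but 170 exceeds the stated minimum by three people. A reader will take it that attrition has been provided for. If it has not, the number with survey outcomes at endline and follow-up can fall below the minimum on which the 80% power rests, even when recruitment meets its goal exactly. The planned difference-in-differences analysis of survey outcomes uses measures from before and after the intervention, so participants who answer only at baseline contribute little to it.

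**Working it through.** **Inputs (Sample size section).** d = 0.25 (f = 0.125); significance level 5%, sidedness not stated; power 80%; required 167 per site and 501 in total over three locations; recruitment goal at least 170 per site. Attrition rates below are assumptions, because the article gives none.

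**Step 1: reproduce 501 and look for a hidden allowance.** For two equal groups and a two-sided test, total N = 4 × ((1.960 + 0.842) / 0.25)² = 502.3, or 252 per group and 504 in total after rounding up. A two-group F test with f = 0.125 gives 505. Both are within 1% of 501. A one-sided test gives 396 and a three-group F test gives 620, and neither matches. The match to 501 uses no attrition allowance, so the provision for loss appears to be only the step from 167 to 170.

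**Step 2: the allowance.** (170 − 167) / 170 = 3/170 = 1.76%, or 1.8%. In total over three sites: (510 − 501) / 510 = 9/510, the same 1.76%.

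**Step 3: what the goal leaves, per site.** Retained = 170 × (1 − a). Recruits needed to keep 167 = 167 / (1 − a), rounded up.

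| Assumed attrition a | Retained from 170 | Recruits needed to keep 167 |
|---|---|---|
| 10% | 153 | 186 |
| 20% | 136 | 209 |
| 30% | 119 | 239 |
| 50% | 85 | 334 |

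**Step 4: power, on one reading only.** Assume 3 × 170 = 510 recruits, two equal groups and no clustering. With n per group = 510 × (1 − a) / 2, power ≈ Φ(0.25 × √(n/2) − 1.96).

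| Assumed attrition a | Analysable total | Power, normal approximation | Power, t test |
|---|---|---|---|
| 20% | 408 | 71.4% | 71.2% |
| 30% | 357 | 65.6% | 65.4% |
| 50% | 255 | 51.4% | 51.1% |

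**Step 5: how far Step 4 depends on its base.** The Study design section lists three treatment and four control municipalities. If each site means all seven, the goal is 7 × 170 = 1,190 recruits, 510 treated and 680 control. At 50% attrition that leaves 255 + 340 = 595, above 501. Unclustered power is then Φ(0.25 × √(255 × 340 / 595) − 1.96) = Φ(3.02 − 1.96), or about 85%. So the totals and powers turn on which sites are counted; the per-site figures in Step 3 do not.

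**Step 6: clustering.** The match in Step 1 also uses no design effect, although an intraclass correlation of 0.04 is stated. With sites as clusters of 167, the conventional factor is 1 + 166 × 0.04 = 7.64. That is a separate question, but it means that the powers in Step 4 cannot stand as the study's actual power.

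**The case against.** The strongest reply is that 170 is worded as a minimum. All students in the selected municipalities are to be invited (Questionnaire instruments), and the endline survey stays open for a couple of weeks while the target number is reached (Phase 3). Recruitment could therefore exceed 170. This stands: a shortfall is conditional on recruitment stopping at the goal. It does not rescue the sentence, because 170 is the only figure offered as the allowance, and a study that stops there meets its goal while missing its own minimum at any loss above 1.8%. A longer endline window can improve response among those enrolled; it cannot supply baseline measures for people who were never enrolled.

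The study is also called a pilot for which a sample size for hypothesis testing is not relevant. That limits the consequence. But the same section sets this number, with 80% power, for a preliminary analysis of impact, and Quantitative analysis of impact makes that assessment the primary aim. A calculation that is given should agree with itself.

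Three stronger readings are tempting and are not supported:

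- **That 80% of participants will be lost.** A reader might infer this from the cited Colombian study. That figure is dropout in another study's intervention, not loss to survey follow-up here. Controls do not receive the platform until the measures are complete, so platform dropout cannot describe them. The same section reports good adherence with the team's own tools. The 80% is context only.
- **That the analysable total will certainly fall below 501, or that the allowance is too small by a factor of ten.** The first requires exactly 510 recruits, which is one reading of the site count. The second requires attrition of about 18% or more, and no rate is stated.
- **That every outcome is affected.** Enrolment, permanence, academic performance, certification and formal employment come from administrative records (Questionnaire instruments), so survey non-response need not remove participants from those analyses.

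**Conclusion.** The stated allowance contradicts the stated expectation. A goal of 170 against a requirement of 167 covers 1.8% attrition, and the sentence presents it as cover for moderately high attrition. This rests on the Sample size section alone and holds whether three or seven municipalities are meant.

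The consequence is conditional. If recruitment stops at the goal, survey attrition above 1.8% takes each site below 167. The drop in power to about 71%, 65% and 51% at 20%, 30% and 50% attrition further assumes 510 recruits in two equal groups and no clustering. It shows the scale of the problem on the basis that reproduces 501, and it is not an estimate of the study's power.

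**What to change.** The text is wrong as written and should be changed in the Sample size section:

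1. State the assumed attrition as a number, separately for the endline and the three-month survey if they differ.
2. Restate the expected analysable number per site and in total, saying which municipalities are counted as sites. For example, if 30% were assumed, 170 recruited per site would yield 119 per site.
3. Give the power or precision at that number, allowing for the stated intraclass correlation of 0.04.
4. Remove the statement that 170 per site allows for moderately high attrition.

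This is a change of wording and a recalculation. No extra recruitment is needed. The cost is that the stated sample and power become less favourable.

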#### Recruitment

Participants in Phases 1 and 2 will be invited via email or in person by JeA program leaders and facilitators. During Phase 3, participants will be invited via email and text messages. Participation is entirely voluntary and will not affect participation in the JeA program. It will be possible for participants to contact researchers directly for further information should they wish not to inform JeA staff of their participation.

#### Inclusion criteria

For all parts of the study, participants must be adults aged 18–28 and registered with the public social program (JeA) living in seven Colombian municipalities affected by the armed conflict. These 7 municipalities are part of the 170 municipalities categorized as “The Development Programs with a Territorial Approach” (PDET in Spanish) by the Havana peace agreement to prioritize social and economic development programs and are the areas most hardly hit by the armed conflict. JeA users are characterized by their low socioeconomic status, according to the National Social Services’ criteria. Many of them are victims of the armed conflict as defined by the victims’ law in Colombia. Participants who meet the inclusion criteria and present anxiety, depression, or post-traumatic stress disorder symptoms will be invited to participate in Phase 3 – piloting the mental health intervention.

#### Study design

Our study is based on a cross-over design, whereby participants in three treatment municipalities (Florencia, Santa Marta, and Valledupar) will be offered the intervention, while participants in four control municipalities (Apartadó, Buenaventura, Ciénega, and San Andrés de Tumaco) will serve as control. Due to ethical reasons, we must offer the intervention to beneficiaries in the control municipalities following the period of intervention in the treatment group. Control municipalities will thus receive the intervention once the two post-treatment measures are taken.

#### Control municipalities

Control municipalities were selected because they share common characteristics with the intervention municipalities in terms of levels of poverty, armed conflict, health, living conditions, public service availability, number of internally displaced people per 100,000, demography, and ethnicity. Additionally, they all have received the “skills for life” training. Control municipalities are also covered by JeA and are PDET territories (conflict-affected areas). To arrive at the control municipalities a proximity score was calculated using the variables with correlations no greater than 0.3 following their standardization (0–1) of their normalized distances.

#### Exclusion criteria

At each phase, if suicidal risk is identified, participants will be referred to the mental health services of their educational institutions or other mental health services in their municipality of residence. They will also be offered access to SilverCloud®. In case of immediate risk to self or others, the consent form will clearly state that we may need to inform the emergency contact participants provide.

